#### Secondary outcomes

Secondary outcomes will include the following:

The Dysphagia Outcome and Severity Scale (DOSS): The DOSS integrates swallowing efficiency and safety. The DOSS scores range from 1 to 7 with 7 grades, and lower scores indicate more severe dysphagia (21). Assessment time frames: at baseline; at week 6.

The Penetration Aspiration Scale (PAS): The PAS focuses on the safety of swallowing. The PAS scores range from 1 to 8 with 8 grades, and higher scores indicate higher risk of penetration and aspiration (22). Assessment time frames: at baseline; at week 6.

The Modified Rankin Scale (mRS): The mRS is a valid and clinically relevant instrument for assessing recovery from stroke (23), and the mRS scores range from 0 to 5 with 6 grades. Assessment time frames: at baseline; at week 2, 4, 6.

The Modified Barthel Index (MBI): The MBI (24) is a common scale for evaluating activities of daily living (ADL), with a total score of 100 points. Assessment time frames: at baseline; at week 2, 4, 6.

Oxygenated hemoglobin and deoxygenated hemoglobin in cerebral cortex: An fNIRS device with wavelengths of 730 and 850 nm (Danyang Hui Chuang Medical Equipment Co., Ltd.) will be used to detect changes in HbO2 and HbR in swallowing-related brain areas during rest and voluntary swallowing. A total of 35 channels will be distributed across the right and left prefrontal cortices (RPFC/LPFC), motor areas (RM1/LM1), somatosensory areas (RS1/LS1), and pre-motor and supplementary motor areas (RPM/LPM). The sampling rate of the fNIRS system will be set to 11 Hz. According to the anatomical positions defined by the international 10–20 system, the probes will be placed on the scalp surface of the subjects based on four reference points (nasal root, external occipital protuberance, left pre-auricular point, right pre-auricular point). A schematic diagram of the probe and channel arrangement is shown in Figure 4 (14). Participants will be seated in a quiet fNIRS assessment room to reduce the impact of noise.

**Figure 4 fig4:**
[figure not shown]
Regions of interest and the channel setting.

During the formal test, the fNIRS device gives start and stop cues at corresponding time points, and the subjects are required to perform swallowing tasks according to the instructions issued by the device. The entire test process consists of 3 identical task blocks, each of which includes 30 s of voluntary swallowing task and 30 s of rest time. During the voluntary swallowing task, the subjects maintain a natural and relaxed state, close their eyes, and perform the repetitive saliva swallowing test task at their own pace.

During the rest period, the subjects are in a natural and relaxed state, close their eyes, remain quiet, and avoid thinking about things unrelated to the experimental task. The schematic diagram of the fNIRS voluntary swallowing task paradigm is shown in Figure 5 (25). The room is kept noise-free and free from external interference. Throughout the entire test process, the subjects always maintain a natural and relaxed state, close their eyes, and complete the corresponding tasks according to the instructions issued by the device. The head and body positions should be kept as still as possible to avoid affecting the fNIRS signal acquisition. Assessment time frames: at baseline; at week 6.

**Figure 5 fig5:**

The experimental procedure.

### Blinding assessment

The Bang’s Blinding Index (26) will be used to assess the adequacy of blinding at week 6.

### Safety assessment

Adverse reactions or adverse events will be recorded in detail, including the time of occurrence of adverse events, symptoms and signs, laboratory examination results, treatment to relieve adverse events, follow-up of adverse events, duration and severity of adverse events. For any serious adverse event occurring during the study (including events causing disability or impact on work ability, life-threatening events or death, etc.), the investigator must take appropriate treatment measures immediately and report to the ethics committee within 24 h or no later than the second working day.

### Data management and monitoring

Data collection and randomization will be handled by the research assistants. The double-input method will be used for data entry, and all data related to patients will be stored confidentially. All researchers and acupuncturists will take a training course before performing the study. The whole process of this trial will be conducted under the supervision of three levels of monitors. The first level of monitors, composed of researchers certified in acupuncture, will be responsible for overseeing the entire study. The second level of monitors, composed of researchers from the ethics committee, will be responsible for study supervision. The third level of monitors, composed of data supervisors, will ensure data authenticity. We have incorporated a comprehensive safety monitoring plan into the protocol: (1) Data Safety Monitoring Board (DSMB): An independent DSMB comprising a neurologist, a stroke rehabilitation specialist, and a biostatistician will be established prior to trial commencement. (2) Pre-specified Stopping Rules: Clear safety stopping rules have been defined, including (a) a significant increase in the rate of symptomatic intracranial hemorrhage beyond expected rates, (b) occurrence of successive serious adverse events related to neurological worsening (increase in NIHSS score by ≥4 points), or (c) a judgment by the DSMB that overall risks outweigh benefits.

### Statistical methods

#### Sample size

This pilot study aims to assess the effectiveness and safety of SMES combined with NGF for dysphagia after ischemic stroke and determine the feasibility of a further definitive trial. To ensure that the clinical trial data have sufficient statistical power, the minimum sample size of each group of subjects should not be less than 30 participants (27). To account for an anticipated 20% dropout rate, the sample size was inflated to 36 participants per group, resulting in a total enrollment of 144 participants.

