### Randomization and allocation concealment

One hundred forty-four eligible participants who have affirmed and signed informed consent will be randomly assigned in a ratio of 1:1:1:1 into the electroacupuncture (EA) + NGF group, the EA + placebo group, the acupuncture + NGF group or the acupuncture + placebo group, each with 36 participants, via a central randomization system, which is managed by a third-party mathematician outside the study and used to generate and conceal the allocation sequence. The randomization sequence will be generated in varying block sizes.

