### Statistical analysis

The overall dropout rate and the dropout rate due to adverse events will be calculated for each group. It will be statistically determined whether each group received the treatment as specified in the study protocol in terms of duration and number of sessions, and the number and percentage of subjects with compliance < 80% will be calculated. Efficacy analysis will be performed in the full analysis set. Participants who have been randomized and have received at least one treatment session will be included in the full analysis set (FAS). All hypothesis tests will be two-sided, and *p*-value < 0.05 will be considered to indicate statistical significance of the tested difference. For ordinal outcomes (FOIS, DOSS, PAS, and mRS), non-parametric tests (Kruskal–Wallis *H* test for group comparisons, with post-hoc Mann–Whitney *U* tests and alpha adjustment) will be used for cross-sectional analyses. For longitudinal ordinal outcomes, generalized estimating equations (GEE) with an appropriate link function (e.g., logit) and working correlation matrix will be the primary method for analyzing these outcomes across multiple time points (FOIS, mRS). The normality of continuous data (MBI, fNIRS metrics) will be assessed using the Shapiro–Wilk test. Provided that parametric assumptions are met, (repeated-measures) ANOVA will be applied. Should the assumptions be violated, non-parametric alternatives (e.g., Kruskal–Wallis test, Friedman test) will be used. The study results will include three-factor (EA factor/NGF factor/time factor) repeated-measure data, with measurement data analyzed using three-factor repeated-measures analysis of variance and ordinal data analyzed using the generalized estimating equation (GEE) to test for differences. The Bonferroni method will be used to adjust for the significance of multiple comparisons.

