There are some limitations to our study. First, as a pilot trial, the sample size is relatively small, which may increase susceptibility to bias. Second, acupuncturists could not be blinded due to the nature of the intervention, potentially introducing performance bias. Third, future studies should incorporate pharmacokinetic sub-studies to optimize the timing between NGF administration and SMES stimulation. Fourth, the SMES parameters (2/100 Hz, 3 mA, 6 s-on/6 s-off) were derived from rodent models. Given biophysical differences between species (e.g., impedance, skull geometry), the intracranial current density in humans requires empirical validation. Future research should use computational modeling, neuroimaging (e.g., dynamic contrast-enhanced MRI), or electrophysiological monitoring for systematic dose-finding. Fifth, while the factorial design distinguishes SMES-specific effects from traditional acupuncture, any observed superiority of SMES + NGF would require confirmation in future trials with strict sham controls and biomarkers before attributing it definitively to BBB-mediated NGF delivery. Sixth, a negative or null result could reflect two distinct possibilities: (1) lack of biological efficacy of the combined intervention, or (2) suboptimal temporal alignment between NGF availability and BBB opening, despite a potentially efficacious mechanism. The current design cannot distinguish between these. Thus, a negative result would highlight the need for further pharmacokinetic-pharmacodynamic studies to optimize intervention timing before concluding on biological plausibility.

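### The 20% dropout allowance is miscalculated: 36 per group leaves 28.8 expected completers, below the plan's own minimum of 30, and the accompanying power claim is unsupported as written

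*Protocol article*

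**What the plan says.** The Sample size section (Statistical methods, protocol article) calls the trial a pilot that assesses effectiveness, safety and the feasibility of a definitive trial. It gives the size in three steps.

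- A floor of 30 per group, supported by a citation and given a purpose: "To ensure that the clinical trial data have sufficient statistical power, the minimum sample size of each group of subjects should not be less than" that number.
- An allowance for loss: "To account for an anticipated 20% dropout rate, the sample size was inflated to 36 participants per group".
- The total: "resulting in a total enrollment of 144 participants".

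The Randomization section repeats 36 per group in a 1:1:1:1 allocation. The Statistical analysis section fixes two-sided tests at 0.05 and analyses efficacy in everyone randomized who had at least one session. The Primary outcome section makes week 6 FOIS the primary endpoint, with FOIS also measured at weeks 2, 4 and 12. The limitations paragraph of the Discussion concedes that "as a pilot trial, the sample size is relatively small".

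**The concern.** Two separate things are wrong in one short section.

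First, the allowance for dropout fails its own test. The section inflates so that losses do not take a group below 30, yet at the stated dropout rate the expected number falls below 30.

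Second, the floor is introduced with the words "To ensure that the clinical trial data have sufficient statistical power", but nothing beside it allows a power figure to be calculated or checked. This is not a detail left to another document: the article makes the claim and offers the count of 30 as its basis.

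What is at stake is how results will be read. The Introduction adopts a 2 × 2 factorial design partly to examine synergy between SMES and NGF. The sixth limitation in the Discussion gives two explanations for a null result, lack of efficacy and poor timing, and does not list imprecision. A reader told that power is sufficient could accept that list as complete.

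**Working it through.** **Inputs from the Sample size section:** floor 30 per group; dropout 20%; 36 per group; 144 in total. **From the Statistical analysis section:** two-sided 0.05. **Not stated anywhere:** effect size, SD, power level, target contrast.

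**1. Reproduce the stated figure.** n × (1 + d) = 30 × 1.20 = 36, and 36 × 4 = 144. Both match exactly.

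**2. Apply the stated dropout.** 36 × (1 − 0.20) = 28.8 per group, which is below 30. In total 144 × 0.80 = 115.2, against 30 × 4 = 120.

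**3. Size that meets the floor in expectation.** n/(1 − d) = 30/0.80 = 37.5, rounded up to 38 per group; 38 × 4 = 152. Check: 38 × 0.80 = 30.4.

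**4. Dropout that 36 can absorb.** 1 − 30/36 = 16.7%.

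**5. Chance of keeping 30 in one group.** If participants drop out independently with probability 20%, the binomial probability of at least 30 completers is 0.40 with 36 enrolled and 0.66 with 38.

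**6. Precision, under assumptions.** The documents give no effect size or SD, so this step treats the outcome as continuous in SD units, at one time point, without baseline adjustment, using the normal approximation. With n per group, the standard errors are √(1/n) for a main effect (2n against 2n), √(2/n) for a pair of groups and √(4/n) for the interaction (a difference of two differences). The 95% half-widths at n = 29 are:

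- main effect: 1.96 × √(1/29) = ±0.36 SD
- pairwise, unadjusted for multiplicity: 1.96 × √(2/29) = ±0.51 SD
- interaction: 1.96 × √(4/29) = ±0.73 SD

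**7. Detectable interaction, same assumptions.** For 80% power at n = 28.8: (1.960 + 0.842) × √(4/28.8) = 1.04 SD. Baseline adjustment multiplies this by √(1 − ρ²): 0.90 SD for an assumed correlation of 0.5, and 0.75 SD for 0.7.

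**8. Does the dropout slip drive interaction power?** Unadjusted power at assumed interactions of 0.5, 0.8 and 1.0 SD:

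| Completers per group | 0.5 SD | 0.8 SD | 1.0 SD |
|---|---|---|---|
| 28.8 (36 enrolled) | 27% | 57% | 77% |
| 30.4 (38 enrolled) | 28% | 60% | 79% |

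Correcting the inflation moves power by 1 to 3 percentage points. The two problems are therefore independent.

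**The case against.** **The shortfall is trivial and the analysis set repairs it.** The gap is 2 per group. The full analysis set keeps anyone with at least one session, and FOIS at weeks 2 and 4 lets many who leave early contribute to the GEE. This stands in part: 28.8 is a count of expected completers, not of participants analysed. It does not remove the error. The section inflates because dropouts are not meant to count towards 30, and someone who leaves before week 6 has no observed value at the primary endpoint.

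**It is a pilot and admits its size.** True, and the admission does not by itself contradict the sample size. Pilot status excuses a small sample. It does not excuse a sum that misses its own target or a power claim with nothing behind it.

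**The basis may lie in the cited source or the full protocol.** Neither is at hand, so nothing is said here about what they contain. The point is limited to the article: as written, it shows no derivation.

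**A stronger reading is tempting: that the trial lacks the power it promises for the interaction.** The documents do not support this. They never tie the power claim to the interaction, which is one of several aims, and they state no effect or power level to fall short of. The detectable effects above rest on assumptions and ignore the 7-point ordinal scale and the repeated measurements. Nor may one say that only very large effects could be seen: under the same assumptions at 28.8 per group, a main effect of 0.52 SD has 80% power.

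**Conclusion.** The inflation is wrong as written. At the plan's own 20% dropout, 36 per group gives 28.8 expected completers against a floor of 30. Meeting the floor in expectation takes 38 per group (152 in total), and 36 suffices only up to 16.7% dropout. This conclusion needs no input beyond the Sample size section. Its size is modest: 2 per group, 8 in total.

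The power claim is unsupported, which is a weaker finding than false. The SD-unit figures show what the design could resolve under stated assumptions. They suggest that a null interaction would leave moderate effects open, but they are conditional and owe almost nothing to the dropout slip.

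**What to change.** 1. **Sample size section.** Keep 36 per group and state that this leaves about 29 completers per group at 20% dropout, or 30 if dropout is at most 16.7%. If 30 completers must be expected at 20% dropout, the alternative is 38 per group and 152 in total, at the cost of 8 more participants.
2. **Same section.** Remove the power claim and state the expected precision: at 29 per group, 95% half-widths of about ±0.36 SD (main effect), ±0.51 SD (pairwise, unadjusted) and ±0.73 SD (interaction), with the assumptions named. If the claim is to stay, give the effect size, variability, power level, test and contrast behind it.
3. **Limitations in the Discussion.** Add imprecision as a third possible explanation of a null result, for the interaction in particular.

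With 36 per group kept, the cost is wording only, and the stated figures become slightly less favourable. No test, endpoint or analysis set changes.

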### Statistical analysis

The overall dropout rate and the dropout rate due to adverse events will be calculated for each group. It will be statistically determined whether each group received the treatment as specified in the study protocol in terms of duration and number of sessions, and the number and percentage of subjects with compliance < 80% will be calculated. Efficacy analysis will be performed in the full analysis set. Participants who have been randomized and have received at least one treatment session will be included in the full analysis set (FAS). All hypothesis tests will be two-sided, and *p*-value < 0.05 will be considered to indicate statistical significance of the tested difference. For ordinal outcomes (FOIS, DOSS, PAS, and mRS), non-parametric tests (Kruskal–Wallis *H* test for group comparisons, with post-hoc Mann–Whitney *U* tests and alpha adjustment) will be used for cross-sectional analyses. For longitudinal ordinal outcomes, generalized estimating equations (GEE) with an appropriate link function (e.g., logit) and working correlation matrix will be the primary method for analyzing these outcomes across multiple time points (FOIS, mRS). The normality of continuous data (MBI, fNIRS metrics) will be assessed using the Shapiro–Wilk test. Provided that parametric assumptions are met, (repeated-measures) ANOVA will be applied. Should the assumptions be violated, non-parametric alternatives (e.g., Kruskal–Wallis test, Friedman test) will be used. The study results will include three-factor (EA factor/NGF factor/time factor) repeated-measure data, with measurement data analyzed using three-factor repeated-measures analysis of variance and ordinal data analyzed using the generalized estimating equation (GEE) to test for differences. The Bonferroni method will be used to adjust for the significance of multiple comparisons.

For the analysis of fNIRS data, preprocessing will be conducted using the NirSpark software package (HuiChuang, China). Initial inspection of raw signals will be performed by an expert to exclude low-quality segments. Motion artifacts in each channel will be corrected through spline interpolation, targeting locally confined signal disruptions. Additionally, a band-pass filter (0.01–0.2 Hz) will be applied to attenuate physiological noise. Subsequent conversion to hemoglobin concentration changes in HbO2 and HbR concentrations will be carried out via the modified Beer–Lambert law (28). The hemodynamic response function (HRF) will be defined with a baseline period of 0–30 s and a task period spanning 30–90 s, extending the analysis window to 210 s. Generalized linear modeling will be applied to the HbO₂ and HbR time-series from each preprocessed dataset. Finally, hemoglobin time series covering 210 s will be extracted for every participant.

The hemoglobin time series for each channel pair will be analyzed using Pearson correlation. Given the normal distribution properties of the z-matrix, the resulting correlation coefficients (*r*) will be converted to *z*-scores using Fisher’s r-to-z transformation prior to further analysis. Based on Brodmann area (BA) classifications, measurement channels will be grouped into four regions: PFC, PM, S1, and M1. Taking into account the bilateral structure of the cerebral hemispheres, a total of eight distinct regions will be defined. An 8 × 8 functional connectivity matrix will then be constructed by independently averaging the z-scores, which will allow for the comparison of functional connectivity across networks.

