**Methods:**

A total of 144 participants will be randomly assigned to an electroacupuncture (EA) + NGF group, an EA + placebo group, an acupuncture + NGF group, or an acupuncture + placebo group in a ratio of 1:1:1:1. Patients will receive 18 sessions of treatment for 6 weeks and a follow up of 6 weeks. The primary outcome is the Functional Oral Intake Scale (FOIS), and the secondary outcomes are the Dysphagia Outcome and Severity Scale (DOSS), the Penetration Aspiration Scale (PAS), the modified Rankin Scale (mRS), and the Modified Barthel Index (MBI). The functional near-infrared spectroscopy (fNIRS) will be applied to detect the changes in neurological function. Additionally, blinding and safety will also be assessed. All analysis will be performed based on intention-to-treat.

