### Blinding

Participants, outcome assessors, and statisticians will remain blinded to treatment allocations. However, as the interventions (acupuncture or EA combined with either NGF or placebo) require direct physical contact with participants, the practitioners administering these interventions cannot be blinded. All participants will be treated separately to prevent communication. Except for acupuncturists, all relevant parties will be blinded to the intervention groups. Participants will be informed that they have an equal chance of allocation to each group before study participation.

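### The abstract promises intention-to-treat for every analysis, but the efficacy set leaves out randomised participants who had no session; two secondary-outcome choices also lose participants

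*Protocol article*

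**What the plan says.** **Analysis set.** The Abstract (Methods) states: "All analysis will be performed based on intention-to-treat". The Statistical analysis section states "Efficacy analysis will be performed in the full analysis set" and then defines that set: "Participants who have been randomized and have received at least one treatment session will be included in the full analysis set (FAS". It describes no other efficacy set. Intention-to-treat is not mentioned again in the body of the article.

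**Who knows the arm.** Under Blinding, participants, outcome assessors and statisticians are blinded, but "the practitioners administering these interventions cannot be blinded".

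**Methods for repeated data.** Continuous outcomes are identified in the sentence "The normality of continuous data (MBI, fNIRS metrics) will be assessed using the Shapiro–Wilk test". Factorial repeated data are to be handled "with measurement data analyzed using three-factor repeated-measures analysis of variance", with Friedman and Kruskal–Wallis tests named as fallbacks. For longitudinal ordinal outcomes, GEE "will be the primary method for analyzing these outcomes across multiple time points (FOIS, mRS").

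**Visits.** Under Outcomes, MBI and mRS are assessed at baseline and weeks 2, 4 and 6. fNIRS is assessed at baseline and week 6. FOIS is assessed at baseline and weeks 2, 4, 6 and 12.

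**mRS scale.** Secondary outcomes: "the mRS scores range from 0 to 5 with 6 grades".

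**Losses expected.** The Sample size section anticipates 20% dropout and enrols 36 per group. The Safety assessment section includes death among serious adverse events.

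**The concern.** Intention-to-treat means that everyone randomised is analysed in the arm assigned. A set that also requires one session makes inclusion depend on something that happens after randomisation. Practitioners know the allocation, so a failure to start need not be independent of the arm. If it is not independent, the comparison is no longer fully protected by randomisation. This applies to every efficacy outcome, including FOIS.

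Two further choices pull away from the same promise, on secondary outcomes only. Conventional repeated-measures ANOVA uses only participants with a value at every visit, so one missed MBI visit removes that participant's other visits too. And a six-grade mRS running from 0 to 5 has no separate place for a participant who dies, so the worst outcome becomes a missing value.

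**Working it through.** **1. Promise against definition.**

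- Abstract: all analyses, intention-to-treat.
- Statistical analysis: efficacy in the full analysis set, which is randomised *and* at least one session.

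A participant randomised and never treated belongs to the first population and not to the second. Both statements are current text. An analysis plan could follow one or the other, but not both.

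**2. How many might be excluded.** The document gives no rate of randomised-but-untreated participants, so this is an assumed range. Excluded = 144 × rate.

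| Assumed never treated | Excluded | Remaining of 144 |
|---|---|---|
| 0% | 0 | 144 |
| 2% | 2.9 | 141.1 |
| 5% | 7.2 | 136.8 |
| 10% | 14.4 | 129.6 |

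**3. Complete profiles under repeated-measures ANOVA.** Inputs: minimum 30 per group, 20% dropout and 36 per group (Sample size); visit schedule (Secondary outcomes).

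- Plan's own figure: 30 × 1.2 = 36 per group, and 4 × 36 = 144. Reproduced.
- Remaining after the plan's dropout: 36 × 0.8 = 28.8 per group, or 144 × 0.8 = 115.2 in all. This is the most that complete-profile analysis can keep at that dropout, and it is below the plan's minimum of 30.
- For MBI, some who stay to week 6 may miss week 2 or week 4. The 20% dropouts are already absent at week 6, so further loss is charged only at the two intermediate visits. Kept = 28.8 × (1 − m)², with m assumed:
  - m = 3%: 28.8 × 0.97² = 27.1 per arm
  - m = 5%: 28.8 × 0.95² = 26.0 per arm
- Share of 36 lost: (36 − 27.1)/36 = 25% to (36 − 26.0)/36 = 28%. Of this, 20 percentage points are the plan's own dropout; the remaining 5–8 points come from intermittent missed visits.
- fNIRS has a single post-baseline visit, so the intermediate-visit loss does not apply. Its ceiling stays at 28.8.

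Friedman's test also needs complete profiles, so this fallback does not remove the problem.

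**4. mRS and death.** Grades 0 to 5 make six, which matches the stated count, so the range is not a slip of arithmetic. It leaves no separate grade for death. A death before week 6, the last mRS visit, therefore has no score on the scale as written. No death rate is given, so the number of participants concerned cannot be computed.

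**The case against.** The strongest reply is that a one-session full analysis set is a common modified intention-to-treat set, that few participants may be affected, and that participants are blinded, so their own withdrawal before the first session cannot follow knowledge of the arm. This stands as a limit on size: only non-starts influenced by practitioners could be related to allocation. It does not reconcile the two statements. Renaming the set modified intention-to-treat in the Abstract would cure the wording but would leave the exclusion in place.

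It is also fair to say that the ANOVA and mRS points are secondary. FOIS and mRS go to GEE, which keeps participants with partial data. Deaths are still recorded and reported as serious adverse events, so they do not vanish from the trial, only from the mRS.

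A reader might go further and infer the following. The document does not support it.

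- *The primary FOIS result is a completers' analysis biased by some number of points.* Any such figure needs one arm to lose its worst swallowers while another loses participants at random. Nothing in the document indicates that asymmetry.
- *GEE will be unweighted and nothing will be imputed.* The article does not say so. These details, and any ranking of death on FOIS, are commonly left to the analysis plan, which is not shown.
- *FOIS collection ends when a participant stops treatment.* No section says this, and FOIS is scheduled at week 12, after the six-week treatment period.

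**Conclusion.** The point holds in three parts of unequal weight.

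- **Main part, all efficacy outcomes.** The intention-to-treat statement and the efficacy set contradict each other. This rests on the text alone. Its numerical effect is unknown: about 3–14 of 144 at an assumed 2–10% never treated, and none if everyone starts.
- **MBI and fNIRS only.** Repeated-measures ANOVA is a poor choice when 20% dropout is expected. At most 28.8 of 36 per arm remain, and about 26–27 for MBI, given the assumed 3–5% missed at each of weeks 2 and 4 and independence of those misses.
- **mRS only.** The stated range has no score for death. The weight depends on the number of deaths by week 6, which is not given.

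These are worth correcting before unblinding, because a choice of analysis set made afterwards could look data-driven. They do not show that the FOIS analysis is biased.

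**What to change.** 1. Define the primary efficacy set as all randomised participants, analysed in their assigned arm. Keep the set with at least one session as a sensitivity analysis. Make the Abstract and the Statistical analysis section agree.
2. For MBI and the fNIRS metrics, replace three-factor repeated-measures ANOVA with a mixed model that has the same EA, NGF and time factors and uses every available visit. The gain is mainly in MBI. With one post-baseline fNIRS visit, a participant who has only a baseline value adds little.
3. Score the mRS 0–6 with 6 = death.

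Cost: changes of wording in the protocol and analysis plan, and modest programming. The downside is a slight dilution of the treatment contrast from the few participants who were never treated; the sensitivity analysis will show its extent.
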